### Relevant concomitant care permitted or prohibited during the trial {11 d}

Except for the study intervention, patients in both groups are treated according to the currently established standard of care at the participating trial centers. Any concomitant care as part of routine clinical practice is permitted.

### Provisions for post-trial care {30}

Parallel to study participation, all study participants receive standard care. This includes extended follow-up after study participation has ended, if necessary. A study insurance for trial-participants is not provided.

### Outcomes {12}

#### Primary outcome

The primary element to be investigated in this study is the postoperative volume development of a primarily surgically relieved unilateral CSDH over the course of 3 months postoperatively. For diagnostic purposes and documentation, cranial cross-sectional imaging using native cMRI or CT-scan and subsequent volumetry to visualize the residual hematoma volume in milliliters will be performed at the planned follow-up time points, 1 day postoperatively, 1 week postoperatively, 1 month postoperatively, 2 months postoperatively and 3 months postoperatively. The volumetry will be performed by a radiologist who is not involved in the study. Although he is not informed about the group assignment of each patient, he is not blinded because the group assignment can easily be identified from the radiological evidence of the embolism material in the imaging. All findings are considered in relation to each other and in relation to the initial findings before the operation. The planned examination intervals correspond to the current standard of care for postoperative imaging follow-up after CSDH surgery and reflect the procedure used in comparable studies [27].

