### Criteria for discontinuing or modifying allocated interventions {11b}

Patients may withdraw their consent at any time without providing a reason and thus terminate their participation in the study prematurely. Withdrawal from the study and reasons, if known, will be documented. Study treatment stops if a surgical treatment for the CSDH is necessary during follow-up, in case of subsequent occurrence of an exclusion criterion or in occurrence of treatment-related complications during treatment. Crossover to the other study arm is not possible after the start of treatment in the respective study arm. Moreover, the principal investigator is entitled to terminate the study prematurely if new scientific findings in favor of one or the other treatment violate the equipoise principle.

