#### Secondary outcome

To answer the question specified in the secondary objective, the need for revision surgery on the primary side of patients included in the study is documented depending on the study arm as well as the time interval to the primary procedure.

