### Sample size {14}

In order to estimate the required sample size, the volume change of a primary operated CSDH under the adjuvant therapy forms to be investigated is analogized with the recurrence rates of primary operated and adjuvant embolized or adjuvant drug-treated CSDH in the literature with regard to the target value defined within the primary objective. For example, the MEMBRANE study, which is currently being recruited, assumes a recurrence rate of 10% when combined surgical and interventional therapy is used [11]. In comparison, the work of Hibahashi et al. [27] puts the recurrence rate of CSDH treated with a combination of surgery and medication at around 2%. Based on this, using the *z*-test for independent samples and an error of the first kind (*α* = 0.05), a sample size of 276 patients (138 per group) is required to achieve a power > 0.8 to detect a difference of 8%.

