## Statistical methods

### Statistical methods for primary and secondary outcomes {20a}

The baseline data and outcome parameters are subjected to a simple descriptive data analysis (median, minimum, maximum and standard deviation in each case; mean only for metrically scaled characteristics).

For difference tests for nominal variables (gender, use of anticoagulation prior to surgery, occurrence of complications due to adjuvant therapy procedures, need for revision surgery), the Pearson chi-squared test is used.

For difference tests of ordinally scaled measured variables (NIHSS, mRS) within the respective groups at different points in time (linked samples), the data collected is tested for normal distribution using the Shapiro–Wilk test. In the case of a parametric distribution, the *t*-test is used for linked samples. In the case of a non-parametric distribution, the Wilcoxon test is used for connected samples (for two-group tests).

For the bivariate dependency analysis of the ordinal scaled characteristics between the two groups at the same point in time, the *t*-test for unconnected samples is used for a parametric distribution and the Mann–Whitney *U*-test for a non-parametric distribution after applying the Shapiro–Wilk test.

For metric variables (hematoma volume), which are subject to a normal distribution, the *t*-test for dependent samples is used to analyze the respective groups at different points in time. In the case of a non-parametric distribution, the Wilcox sign-rank test is used for the analysis.

For the bivariate dependency analysis of the metric characteristics between the two groups at the same point in time, after applying the Shapiro–Wilk test, the *t*-test for unrelated samples is used for a parametric distribution and the Mann–Whitney *U*-test for a non-parametric distribution.

In addition, a logistic regression is tested with the revision rate as the dependent variable and the treatment groups and baseline data as independent variables.

Furthermore, a correlation analysis of the relationship between the postoperative volume size and the revision rate as well as the postoperative neurological assessment and the revision rate is performed, in each case for mixed scaling pairs with the chi-squared test. The respective singular correlation analysis is followed by an analysis of the existence of a partial correlation between the two parameters in relation to the revision rate.

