### Methods in analysis to handle protocol nonadherence and any statistical methods to handle missing data {20c}

Missing data will be avoided as much as possible by planning scheduled visits well in advance. If a significant amount of data is missing for any of the primary endpoints or other analyses, we will conduct exploratory analyses to assess the impact of the missing data, according to the EMA-guidelines [4]. Depending on the amount of missing data, it will be assessed whether missing covariates can be replaced by multiple imputation with predictive mean adjustment.

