### Adverse event reporting and harms {22}

Adverse events are defined as any undesirable experience occurring to a subject during the study, whether or not considered related to the investigational product (TXA) or investigational intervention (embolization). After participants have provided consent and been enrolled in the study, adverse events or complications of the treatment, will be documented and recorded until the end of the study period. Any serious adverse event that occurs in this trial will be reported to the principal investigator (PI). The PI must decide whether the participant can continue to participate in the study or whether he or she has to be excluded. The study team in every participating center will take responsibility for the treatment of the trails related adverse events or complications. The PI of the study will consider the continuation or discontinuation of the research under the following circumstances:◦ If a serious adverse event or disease report suggests that continuing the study poses safety concerns◦ If recruiting participants for the study becomes challenging, making it difficult to achieve the planned number of cases◦ When significant new information regarding the quality, safety, or efficacy of the medication (TXA) and interventional procedure (embolization) is obtained

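### No rule separates scans taken after revision surgery, so treatment failures enter the later between-arm volume comparisons with surgically reduced volumes

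*Protocol article*

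**What the plan says.** - **Outcome.** Under Primary outcome: "The primary element to be investigated in this study is the postoperative volume development of a primarily surgically relieved unilateral CSDH". Residual volume in ml is measured at "1 day postoperatively, 1 week postoperatively, 1 month postoperatively, 2 months postoperatively and 3 months postoperatively". The times count from the primary operation, with no exception for a patient who is operated on again.
- **Revision.** Under Secondary outcome: "the need for revision surgery on the primary side of patients included in the study is documented depending on the study arm". It is a separate outcome, but on the side whose volume is the primary outcome.
- **What revision changes.** Criteria for discontinuing {11b}: "Study treatment stops if a surgical treatment for the CSDH is necessary during follow-up". Nothing there ends visits, imaging or use of the scans.
- **Test.** Statistical methods {20a}, "For the bivariate dependency analysis of the metric characteristics between the two groups at the same point in time", uses a t-test or a Mann-Whitney U-test, depending on a Shapiro-Wilk test. Revision enters only as its own outcome and in a correlation with volume.
- **Missing data.** Section {20c}: "If a significant amount of data is missing for any of the primary endpoints or other analyses, we will conduct exploratory analyses". A scan after revision is not missing, so this does not reach it.
- **Exclusion after a serious adverse event.** Section {22}: "The PI must decide whether the participant can continue to participate in the study or whether he or she has to be excluded". This concerns participation in the study, not only treatment.
- **Aim.** The Abstract and Trial design {8} ask whether the two treatments are equivalent in volume reduction and need for revision.

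**The concern.** A patient whose hematoma recurs and is evacuated again has had a clear failure of the adjuvant treatment. At the next visit the scan shows what the second operation left behind, and {20a} tests that value like any other. The more failures an arm has, the more of its large volumes are replaced in this way.

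This touches the contrast on which the trial was sized. Sample size {14} treats volume change as analogous to recurrence and takes 10% in the embolization arm against about 2% with tranexamic acid. Large volumes due to recurrence are what revision removes before the 3-month scan. Because the stated aim is equivalence, a contrast that shrinks for this reason would be read as support for the conclusion sought.

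Section {22} adds a separate route. In an open-label trial the principal investigator may exclude a patient from the study after a serious adverse event, and the later volumes of such patients would then be absent.

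**Working it through.** **1. The plan's own figure.** Inputs from Sample size {14}: 10% and 2%, alpha 0.05, power above 0.8. Two-sided z-test, pooled variance under the null, no continuity correction:

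n = [1.960 × √(2 × 0.06 × 0.94) + 0.842 × √(0.10 × 0.90 + 0.02 × 0.98)]² / 0.08² = (0.658 + 0.279)² / 0.0064 ≈ 137.2, so 138 per arm. Power at 138 is 0.802. The stated 276 is reproduced.

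**2. Expected revisions on those rates,** taking each recurrence as revised: 138 × 0.10 = 13.8 (embolization) and 138 × 0.02 = 2.8 (tranexamic acid).

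**3. Failures' contribution to the mean difference.** With equal non-recurrent volumes in both arms, it is (0.10 - 0.02) × (mean volume of failures - mean volume of non-failures). Revision changes only the first mean.

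The article gives no volumes, so these are assumptions: non-recurrent volume lognormal, median 10 ml, log-SD 0.9 (mean 10 × exp(0.405) ≈ 15.0 ml); recurrent and not revised, mean 90 ml (SD 25); after revision, lognormal with median 5 to 20 ml and the same log-SD (mean 7.5 to 30.0 ml).

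- Not revised: 0.08 × (90 - 15.0) = 6.0 ml.
- After revision, median 5 ml: 0.08 × (7.5 - 15.0) = -0.6 ml.
- After revision, median 10 ml: 0 ml.
- After revision, median 20 ml: 0.08 × (30.0 - 15.0) = +1.2 ml.

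Simulated values run from -0.6 to +1.3 ml; a log-SD of 1.0 gives -0.7 to +1.3 ml.

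**4. Mann-Whitney test at 3 months,** simulated with 138 per arm and 10% v 2%; ranges are over the post-revision medians.

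| Non-recurrent volumes | Post-revision scans used | Revised patients left out | Revision ranked worst |
|---|---|---|---|
| Equal in both arms | 5-9% | about 5% | 20-23% |
| 25% higher with embolization (12.5 v 10 ml) | 26-64% | about 50% | 83-85% |

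The second row depends on the spread. At log-SD 0.8, use of post-revision scans gives 30-73% against 88-89% with worst rank; at 1.0 it gives 23-56% against about 79%.

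**5. Different assumptions.** Normal volumes floored at 0, non-failures about 30 ml (SD 20), failures 70 or 100 ml unrevised and 15 or 30 ml after revision:

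- Equal non-failures: the mean difference falls from 3.1-5.6 ml to between -1.3 and 0 ml, and t-test rejection from 0.23-0.47 to 0.05-0.09.
- 5 ml shift among non-failures: the difference falls from 7.6-10.1 ml to 3.2-4.5 ml, and t-test power from 0.86-0.93 to 0.31-0.52. A Mann-Whitney test with revision ranked worst gives 0.83-0.85.

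Both sets of assumptions show the same attenuation.

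**The case against.** **The text does not say that post-revision scans are analysed, and a full protocol or analysis plan may add a rule.** That stands as a limit. It is the default reading: every planned visit is compared, only treatment stops, and nothing sets later scans apart. The article does fix the outcome, the visits and the tests. Leaving revised patients out would not help, as step 4 shows.

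**Failures are not hidden.** True: revision and its timing are the secondary outcome, tested by chi-squared and logistic regression. That does not repair the primary comparison, which could show no difference while the secondary outcome shows one.

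**Stronger readings that a reader might infer, and that the documents do not support:**

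- *The 3-month test is no better than chance.* This holds only if non-recurrent volumes are equal and post-revision volumes match them. The primary objective is volume decrease in all patients, and {14} uses recurrence as an analogy. It does not say that the whole volume effect lies in recurrences.
- *The worse arm would look better.* A reversal needs post-revision volumes below non-recurrent ones. No volumes are given.
- *Patients who die drop out of the analysis.* The article does not say this.
- *Section {22} removes recurrences.* It speaks of serious adverse events and does not mention revision.

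**Worst rank has costs of its own.** This stands. Under {17a} physicians are unblinded, so the ranking brings an unblinded decision to re-operate into the primary outcome.

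**Conclusion.** The concern holds. As written, the plan lets a second evacuation stand in for the effect of the adjuvant treatment in every volume comparison after revision. The later contrast is attenuated if revision rates differ between arms, as the protocol's own 10% v 2% implies; with equal rates the volumes are distorted but the arms are not pulled together for this reason. Scans before revision are unaffected.

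The direction follows from the article. The size does not: every ml and rejection figure rests on assumed volumes and shows only that the loss can be large. Since attenuation favours the equivalence conclusion, the handling should be settled before analysis.

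**What to change.** 1. **Primary comparison.** In the 3-month between-arm volume comparison, rank patients with revision surgery or death worst and use the Mann-Whitney test already named in {20a}. Report observed volumes in ml, post-revision scans included, as a supportive analysis. Downsides: a ranked composite has no direct ml estimate, overlaps with the secondary outcome and includes an unblinded decision to re-operate, so both analyses should be shown. It also does not guarantee power (20-23% in the equal-volume scenario).
2. **Section {22}.** Separate the decision on study treatment from study participation. After a serious adverse event, treatment stop or revision, the patient stays in scheduled follow-up and in the analysis unless consent is withdrawn.
3. **Minor.** The mRS list under Tertiary outcome ends at 5. Add the death category so that deaths count in the neurological outcome.

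Cost: no new data, since revision timing and scans are already collected. Recruitment began in May 2024, so the change needs the amendment route in {25}: ethics committees, participating centers and the registry.

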### Strategies to improve adherence to interventions {11c}

Test group:

Treatment as part of the study takes place within 3 months of inclusion in the study. Follow-up visits will take place after 1, 4, 8, and 12 weeks. Upon enrollment in the study, the participant will receive instructions on how to take the medication, including when to take it, how to store it, the importance of taking the capsules as a whole and what to do in the event of a missed dose. The importance of adhering to the study protocol is also discussed.

At the follow-up visits, compliance with the treatment is monitored by asking whether the medication was taken regularly at the prescribed times, at what times the capsules were taken and whether the participant experienced any side effects. Study participants are asked to contact one of the researchers if they have any questions about the study medication during the treatment period. Medication monitoring will be performed by one of the researchers or by the research nurse who will also perform the follow-up measurements. The reason for any non-compliance will be recorded on the designated case report form.

2.Control group:

There is no possibility to influence patients’ adherence in that study group to the intervention. Embolization of the MMA constitutes the only study intervention, which is solely performed by the clinical investigators.

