## Assignment of interventions: blinding

### Who will be blinded {17a}

Due to the study design, which compares a drug therapy with an interventional procedure, neither the patients nor the physicians can be blinded. In addition, the embolizate used in the embolization of the patients treated in the control group will always be visible in the imaging control examinations in both MRI and CT, so that neither the radiologist nor the neurosurgeon can be meaningfully blinded here.

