**Fig. 2 Fig2:**
[figure not shown]
Preoperative volume measurement of a right-sided hemispheric chronic subdural hematoma using the CT data set

The following intervention-associated complications will be documented as part of the study:Vascular dissections caused by the guidewireDislocation of embolized materialIschemia caused by vascular occlusion during the interventionInflammation or abscesses at the puncture siteVascular fistula in the area of the puncture siteRetinal blindnessEpidural hematomas after perforation of the meningeal arteryAllergic reactions to the contrast mediumAcute renal failure

The following complications or adverse events associated with the use of tranexamic acid will be documented:Intolerance reactionsPulmonary embolismsVenous thrombosisEpileptic seizuresMyocardial infarctionsCerebral ischemic infarctionsAcute renal failure

All research data, including baseline data (NIHSS, mRS, hematoma volume, patient demographics and characteristics) prior to surgery, will be collected anonymously in an electronic data collection form at each study center. The PI of the trial summarizes these for all centers and exports data for statistical analysis. All investigators will be trained to perform outcome measurements and will be introduced to the data management prior to recruitment of the first patient.

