### Plans to promote participant retention and complete follow‐up {18b}

Participants will be informed about the study’s objective and relevance. The importance of completing the treatment and the follow-up evaluation, both for the study’s quality and for their personal chance to benefit from the therapy, will be emphasized. Participating patients are consciously informed that there are no personal benefits to take part in the study. Nevertheless, it is also explained that there is scientific evidence that patients who are treated as part of a clinical trial can obtain better results than patients who are treated under routine conditions.

Study follow-up is performed at 1 week and 1, 2, and 3 month (± 1 week) after evacuation of the hematoma with an outpatient clinic visit and CT or MRI scans. During these visits, all outcome measurements are performed by one of the researchers. To maximize participant retention, this study follow-up is parallel to the regular follow-up in the outpatient clinic (standard treatment). In addition, appointments for follow-up examinations are made as soon as the patient is discharged from inpatient treatment in order to increase compliance with participation.

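### The primary hematoma volume is read by someone who can recognise embolized patients, and the follow-up text as written has researchers make all outcome measurements, so reader bias can enter the primary comparison

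*Protocol article*

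**What the plan says.** Under Outcomes {12}, Primary outcome, the endpoint is hematoma volume in millilitres from CT or native MRI: "subsequent volumetry to visualize the residual hematoma volume in milliliters will be performed at the planned follow-up time points". The same paragraph names the reader: "The volumetry will be performed by a radiologist who is not involved in the study". It adds that he is not informed of the allocation, and then that "he is not blinded because the group assignment can easily be identified from the radiological evidence of the embolism material". The section Who will be blinded {17a} repeats this for both modalities, "so that neither the radiologist nor the neurosurgeon can be meaningfully blinded here".

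Three other places say who measures outcomes:

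- Section {18a}/{19}, in the text after Fig. 2: "All investigators will be trained to perform outcome measurements". The same section says that volume is measured with an image viewing program, without naming the reader.
- Section {18b}, on the outpatient visits with CT or MRI at 1 week and 1, 2 and 3 months: "During these visits, all outcome measurements are performed by one of the researchers".
- Section {11c}, for the test group: medication monitoring is done "by one of the researchers or by the research nurse who will also perform the follow-up measurements".

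Nothing in the article links these statements to the outside radiologist.

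**The concern.** Two things come together here.

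First, the primary measurement depends on outlining a hematoma on an image, and the person doing it can tell who was embolized. The article records this as unavoidable and states no reading procedure that would limit its effect.

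Second, the general wording in {18b} and {18a}/{19} leaves it open whether a study researcher may supply the volume. Such a researcher is not merely able to guess the allocation but knows it.

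At stake is the validity of the comparison of volumes between arms. A consistent tendency to outline more tightly in one arm looks exactly like a treatment effect, and recruiting more patients does not remove it. The article asks whether the two treatments are equivalent, so a shift in the opposite direction matters too, because it could hide a real difference.

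**Working it through.** **Who reads the volume.** Side by side:

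| Place | Who measures | Volume named? |
|---|---|---|
| Primary outcome {12} | radiologist outside the study, not told the allocation | yes |
| {18a}/{19} | investigators trained for outcome measurements | volume described, reader not named |
| {18b} | one of the researchers, all outcome measurements at visits with imaging | not by name, but included in all outcomes |
| {11c} | researcher or research nurse who also monitors tablet intake | no |

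The first and third rows cannot both be literally true. Limiting {18b} to NIHSS and mRS would reconcile them, but the text does not do so.

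**Which scans reveal treatment.** Preoperative scans cannot show embolic material, nor can a day-1 scan taken before embolization. Embolization may take place at any time within 72 h of surgery, so some day-1 scans may already show it. All later scans of embolized patients may show it. Because crossover is allowed, visible material indicates the treatment received, which is not always the arm assigned.

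**The plan's own figure.** Section {14} gives 138 per group for 10% against 2% with α = 0.05 and power above 0.8. With a two-sided z-test and pooled variance (mean proportion 0.06):

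n = [1.96·√(2·0.06·0.94) + 0.8416·√(0.10·0.90 + 0.02·0.98)]² / 0.08² = (0.658 + 0.279)² / 0.0064 ≈ 137.2, rounded up to 138.

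The figure reproduces, with power 80.2%. It is built on recurrence rates and so says nothing about volume or reading error.

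**What a reading shift would do.** Inputs: 138 per arm ({14}), a two-sided 5% test between groups at one visit ({20a}), and no true difference. The shift b between arms is in units of the SD of volume. It is an assumption, because the document gives neither an SD nor a shift.

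- SE = √(2/138) = 0.120 SD
- P(p < 0.05) = Φ(−1.96 − b/SE) + 1 − Φ(1.96 − b/SE)

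| Assumed shift b | b/SE | P(p < 0.05) with equal treatments |
|---|---|---|
| 0 | 0 | 5% |
| 0.05 SD | 0.42 | 7% |
| 0.10 SD | 0.83 | 13% |
| 0.20 SD | 1.66 | 38% |

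For scale, the true difference detectable with 80% power is (1.96 + 0.84)·0.120 ≈ 0.34 SD. A shift of 0.10 SD against that difference leaves 0.337 − 0.10 = 0.237 SD. Then 0.237/0.120 ≈ 1.97, and power falls to Φ(1.97 − 1.96) ≈ 50%.

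**The case against.** The other side has several good points.

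- **The primary outcome section is the specific rule.** Section {18b} is about retention and describes clinic visits. {18a}/{19} assigns NIHSS and mRS to the clinical investigators and describes volume separately. A reader might infer that the protocol gives volumetry to site staff. No place says so by name, and the clinical scores are a plausible intended meaning. What stands is that the word all, as written, includes the primary outcome.
- **The plan does take steps.** A reader might infer that nothing is done to limit bias. In fact the radiologist is outside the study and is not told the allocation. Both steps help, but neither works once embolic material is visible.
- **A condensed article need not carry a reading manual.** That is fair, and the lack of such detail is not the point. The article states affirmatively that the reader is not blinded and accepts it, and that stated choice can be improved.
- **The percentages follow from assumed shifts** and would fit any continuous outcome with 138 per arm read without blinding. This is correct. They show sensitivity and are not an estimate for this trial.
- **Embolic material cannot simply be removed from the images.** A density window does not carry over to MRI. The material lies in vessels of the dura, next to the hematoma, so cropping could alter the images of embolized patients only and create a difference between arms. This stands in full, and the fix does not use that step.

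**Conclusion.** The point holds in a limited form. The article accepts primary volumetry by a reader who can identify embolized patients, and its follow-up sections, as written, conflict with its choice of an outside reader. Reader bias can therefore enter the primary comparison.

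The tempting stronger conclusion, that the primary result will be biased, is not supported. The document gives no volume SD, no information on reading error and no reason to expect a shift in either direction. The lack of blinding is also disclosed openly.

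The size is conditional. If shifts of 0.05 to 0.20 SD are assumed, the 5% error at a single visit becomes about 7% to 38%, against a detectable difference of about 0.34 SD. The change is worth making because it is cheap and protects the primary endpoint.

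A secondary point concerns the tertiary outcomes. Under {11c} the person who asks about tablet intake also takes the follow-up measurements, which gives the NIHSS and mRS rater an avoidable cue. Patients are not blinded and may reveal their treatment anyway, so the gain here is modest.

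**What to change.** 1. **Settle the reader.** State in {18a}/{19} and {18b} that volumetry follows the primary outcome section and that only the outside radiologist's volumes are used for the primary outcome. Limit researchers' measurements at visits to NIHSS, mRS and other clinical data.
2. **Fix the reading procedure in the primary outcome section.** The same radiologist reads scans stripped of identifiers and visit dates, under one segmentation rule (semi-automated where possible) applied identically in both arms. He first reads the preoperative scans and those day-1 scans taken before any embolization, as a batch that carries no information on arm. All later scans are then pooled across patients and visits and read in random order, and he records for each whether embolic material was evident. Someone other than the reader assembles the batches. Do not require density-window removal or cropping of embolic material.
3. **Secondary.** In {11c}, have NIHSS and mRS scored before tablet intake is asked about.

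Cost: protocol wording, image preparation, and transfer of images between centers, for which the confidentiality section {27} already requires a data transfer agreement. Study volumes become available later. Masking remains incomplete on later scans. No additional reader or patients are needed. Recruitment has started, but scans already acquired can still be read under this procedure.
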